## Abstract

**Background:**

To reduce mortality, women with a family history of breast cancer often start mammography screening at a younger age than the general population. Breast density is high in over 50% of women younger than 50 years. With high breast density, breast cancer incidence increases, but sensitivity of mammography decreases. Therefore, mammography might not be the optimal method for breast cancer screening in young women. Adding MRI increases sensitivity, but also the risk of false-positive results. The limitation of all previous MRI screening studies is that they do not contain a comparison group; all participants received both MRI and mammography. Therefore, we cannot empirically assess in which stage tumours would have been detected by either test.

The aim of the Familial MRI Screening Study (FaMRIsc) is to compare the efficacy of MRI screening to mammography for women with a familial risk. Furthermore, we will assess the influence of breast density.

**Methods/Design:**

This Dutch multicentre, randomized controlled trial, with balanced randomisation (1:1) has a parallel grouped design. Women with a cumulative lifetime risk for breast cancer due to their family history of ≥20%, aged 30–55 years are eligible. Identified BRCA1/2 mutation carriers or women with 50% risk of carrying a mutation are excluded. Group 1 receives yearly mammography and clinical breast examination (n = 1000), and group 2 yearly MRI and clinical breast examination, and mammography biennially (n = 1000).

Primary endpoints are the number and stage of the detected breast cancers in each arm. Secondary endpoints are the number of false-positive results in both screening arms. Furthermore, sensitivity and positive predictive value of both screening strategies will be assessed. Cost-effectiveness of both strategies will be assessed. Analyses will also be performed with mammographic density as stratification factor.

**Discussion:**

Personalized breast cancer screening might optimize mortality reduction with less over diagnosis. Breast density may be a key discriminator for selecting the optimal screening strategy for women < 55 years with familial breast cancer risk; mammography or MRI. These issues are addressed in the FaMRIsc study including high risk women due to a familial predisposition.

**Trial registration:**

Netherland Trial Register NTR2789

## Background

A positive family history is one of the most important risk factors for breast cancer
[1]. Women with a family history of breast cancer are not only at greater risk of developing breast cancer, but their risk also increases at a younger age than in the general population
[2]. In over 75% of the families that display clear clustering of breast cancer no causative gene mutation like BRCA1 or BRCA2 can be detected
[3]. Tumour stage at detection is of key influence on survival
[4]. Aiming at early detection and ultimately to reduce mortality risk, women, with a positive family history for breast cancer, are often offered annual screening with mammography before age 50
[5-7]. However, screening also causes false-positive test results.

In the last decade several screening trials in high-risk women have been completed and Magnetic Resonance Imaging (MRI) had a significantly higher sensitivity for invasive breast cancer than mammography in all studies
[8-12]. However, MRI was expensive and was associated with significantly more false-positive results in most studies. Furthermore, mammography had better sensitivity for the pre-invasive stage of breast cancer: ductal carcinoma in situ (DCIS)
[13]. Therefore, mammography should perhaps not be omitted completely when MRI screening is offered.

Despite the higher costs of MRI and the false-positive results, screening with yearly MRI in addition to mammography is considered cost-effective for female *BRCA1* and *BRCA2* gene mutation carriers aged 30–60 years or women who have a 50% chance of carrying such a mutation
[14-16]. For women with a familial risk, from families without a proven genetic predisposition, results are inconclusive
[17,18]. Since previous screening studies have performed MRI and mammography simultaneously the difference in stage of the tumours when detected by mammography alone is not known. A randomized controlled trial is therefore needed.

Apart from a positive family history and age, high breast tissue density is a well documented risk factor for breast cancer. Breast density increases breast cancer incidence significantly
[19,20]. At the same time, high mammographic density impairs the sensitivity of mammography
[19-22], but far less the sensitivity of MRI
[23]. The lower sensitivity of mammography in dense breasts is most likely caused by a masking effect, rather than by a higher tumour growth rate in denser tissue
[21,24]. Breast density is high or very-high in about 50-74% of women between 40 to 49 years of age, whereas only 20-44% of women in their 60s have dense or extremely dense breast tissue
[25,26]. This dual effect of breast density on cancer incidence and sensitivity of mammography results in women with the highest risk being screened with a tool with limited effectiveness: mammography.

To the best of our knowledge, no study has been published assessing the cost-effectiveness of MRI specifically in women with a familial risk for breast cancer, without a known genetic predisposition. Therefore, guidelines for breast cancer screening for women with a familial risk vary widely internationally and are weakly underpinned. The 2008 American Cancer Society and 2010 American College of Radiologists guidelines advise MRI screening for women with a familial cumulative lifetime risk (CLTR) > 20%
[18], while the Dutch guidelines advise screening with mammography only
[17].

Robust cost-effectiveness analyses cannot be based on the published studies, as all had a paired design (i.e. all participants received both mammography and MRI). These studies cannot examine the improvement in tumour stage at diagnosis, as one cannot know in what stage the tumour would have been diagnosed by either test alone. A randomized controlled trial is needed for a valid answer to these questions.

Furthermore, cost-effectiveness of either imaging technique may vary across categories of mammographic density. Breast density has not yet been evaluated as a parameter to identify sub-groups of women with a familial risk, for whom MRI is cost-effective. A prospective randomized trial in women with increased breast cancer risk, taking breast density into account, will give robust evidence on which screening tool, MRI or mammography, is best suited for a particular woman. These issues are addressed in the Familial MRI Screening study (FaMRIsc).

## Methods/Design

### Trial design

The FaMRIsc study is a multicentre, randomized controlled trial (RCT), with balanced randomisation (1:1), and a parallel group design conducted in the Netherlands. The study is in compliance with the Helsinki declaration and ethical approval has been granted on 8 November 2010 by the Institutional Review Board of the Erasmus University Medical Centre, Rotterdam, the Netherlands (reference-number: MEC-2010-292).

### Participants

Eligible participants are women aged 30–55 years with a cumulative lifetime risk (CLTR) of >20% because of a familial predisposition according to the modified tables of Claus
[1,27] or as assessed at a Clinical Genetics Centre. *BRCA1* and/or *BRCA2* mutation carriers or women with a 50% likelihood of such a mutation are excluded, since MRI screening is already advised for these women by the American Cancer Society (ACS), the American College of Radiologists (ACR), the United Kingdom’s NICE guideline and the European guideline of the European Society of breast imaging (EUSOBI)
[18,28-30]. Exclusion criteria are previous invasive cancer (potentially of influence on survival data), and a contraindication for contrast-enhanced MRI (decreased creatinin clearance, metal implants or claustrophobia).

### Study settings

Participants are recruited from outpatient breast or family cancer clinics at all eight academic medical centres in the Netherlands and the Netherlands Cancer Institute/Antoni van Leeuwenhoek Hospital (
Additional file 1). Women who are already in a screening programme because of an increased familial risk and meeting inclusion criteria are sent study information 2 weeks before a scheduled visit. Women who meet all criteria and visit the outpatient clinic for an initial screening are given information on site.

### Interventions

After informed consent is obtained participants are randomized through a computer-generated randomization sequence with stratification for centre, in one of the two groups.

Group 1 receives screening according to the 2012 Dutch guidelines
[17] with yearly mammography and clinical breast examination (CBE).

Group 2 is screened with yearly MRI and CBE, and mammography biennially (Figure
1). Additional investigations are performed if deemed necessary due to findings at clinical examination, on mammography or MRI. Mammography still has a place in both arms, since DCIS is generally easier to detect with mammography
[8,10,31-33], although in one study MRI was found to detect more aggressive grade III DCIS than mammography
[34]. In the intervention arm however, the frequency of mammography is reduced from annually to biennially. DCIS not detected by MRI will most likely be low-grade, progress slowly, and be detected by the next mammographic examination. Leaving out mammography every other year seems safe in the MRI arm and may prevent over diagnosis of low-grade DCIS. Mammographic examination is done using full field digital mammography (FFDM). All examinations are scored in a standardized way, according to the Breast Imaging Reporting and Data System (BI-RADS) mammography classification of the American College of Radiology
[30]. To determine mammographic density an automated breast density measurement is done on raw data of the first FFDM of all participants
[35,36]. Dynamic breast MRI with gadolinium-containing contrast medium is performed according to standard protocol. In premenopausal women, the MRI is performed between day 5 and 20 of the menstrual cycle
[37]. 

**Figure 1 F1:**
[figure not shown]
** Flow diagram Familial MRI Screening Study (FaMRIsc).** CLTR: *Cumulative Lifetime Risk,* MRI: *Magnetic Resonance Imaging*, CBE: *Clinical Breast Examination*.

### Outcomes

Primary endpoints are the number and stage of detected breast cancers, both DCIS and invasive, in each arm. Secondary endpoints are the false-positive results in the screening arms, and the sensitivity and positive predictive value of both screening strategies. Furthermore, cost-effectiveness and breast cancer mortality reduction of both strategies will be assessed. All analyzes will also be performed stratified for mammographic density.

A positive screening test is defined as a mammographic or MRI examination with a BI-RADS score of 0, 3, 4, or 5 and/or a clinical breast examination classified as ‘suspicious’. Interval cancers are defined as tumours diagnosed after a negative screening examination but before the next scheduled screening examination. Sensitivity is calculated as the number of screen-detected tumours divided by the total of screen-detected and interval tumours. The positive predictive value of a screening strategy is calculated as the proportion of women with a positive screening test, which after pathology indeed proved to be breast cancer.

Prospective assessment of mortality reduction requires a very lengthy follow-up and a large study population, which may not be feasible. To study this issue we will start with a less costly and time-consuming approach and estimate mortality reduction through a micro-simulation model: MISCAN, a well-validated micro-simulation model, originally developed to estimate the cost-effectiveness of the population-based screening program in the Netherlands
[38-40]. In the model, the natural history of breast cancer is modelled as a progression through 5 pre-clinical and invasive disease stages. At each pre-clinical stage, a tumour may either be clinically diagnosed or grow into the next pre-clinical stage. Screening may detect the tumour in a preclinical stage. Transition probabilities, stage durations and survival after clinical diagnosis or screen detection are based on data from the Dutch nation-wide screening program
[41,42]. The improvement of prognosis after detection by screening is based on the long-term effects of Swedish trials
[43-45]. A detailed description of the model has been published previously
[39].

We will develop a family history risk model by using the number of women enrolled in the study, the age distribution at entry of the study, the duration of follow-up and the screening protocol, attendance and sensitivity of different screenings methods as inputs. The model will be calibrated using the number of screens, the number of screen detected cancers and interval cancers, the stage distribution and the age at diagnosis. Likelihood ratio tests will be used to compare the goodness of fit. Using the calibrated model, predictions of the number of screens, number of screen detected and interval cancers, the stage distribution, the mortality reduction and the life years gained will be made for the different screening arms in the study.

A cohort of 5 million women will be simulated. All costs and effects will be predicted for a life-time follow-up. The costs will be presented in European currency (€). Cost-effectiveness ratios will be expressed as cost per life year gained (LYG). Costs and effects will be discounted at an annual rate of 3.5%.

### Sample size/power calculation

Our primary aim is to detect a difference in tumour stage between the intervention and the current practice group. In the Dutch MRI Screening Study (MRISC) study, conducted from 1999 to 2007, over 1500 women with familial risk were included in the 6 participating centres
[11]. The incidence rate in this risk group was 7/1000 women years screened. Since the FaMRIsc study will have three more participating centres we intend to include 2000 women. We expect to detect about 50 breast cancers (both DCIS and invasive) in 4 years. With this number we are able to detect a difference in tumour size of 8 mm (SD tumour size: 9 mm) as statistically significant (two sided alpha =0.05) with a power of 80%. Eight mm is considered to be a clinically relevant difference.

### Stopping guidelines

The accrual will be evaluated after two years. If adequate inclusion numbers cannot be achieved, appropriate measures will be taken in the remaining two years, consisting of expansion of the number of participating centres or longer continuation of the study.

### Statistical methods

Primary outcome will be incidence and the difference in mean tumour size at diagnosis between the two arms. If normally distributed, this will be tested by means of the independent samples (unpaired) *t*-test. If not normally distributed, medians will be estimated and differences between distributions will be tested with the non-parametric Mann–Whitney *U* test.

Breast cancer incidence rates will be calculated as the total number of breast cancers detected per 1000 woman-years at risk. This will be calculated both including and excluding DCIS. Differences between these proportions will be compared using a chi-square test or Fisher’s exact test as appropriate.

All tests will also be performed stratified by mammographic density to examine the influence of density on the efficacy of MRI screening versus usual care. The influence of breast density on detection rates, tumour stage and false positive results in both arms will be analysed by means of analysis of variance (ANOVA).

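### The powered primary test compares tumour size only among women with a diagnosed cancer, so extra small tumours found in the MRI arm can lower the mean with no larger cancer averted

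*Protocol article*

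**What the plan says.** The protocol article describes the primary comparison in three places.

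- **Outcomes:** "Primary endpoints are the number and stage of detected breast cancers, both DCIS and invasive, in each arm".
- **Sample size/power calculation:** "Our primary aim is to detect a difference in tumour stage between the intervention and the current practice group". The power statement that follows concerns tumour size only: 8 mm, SD 9 mm, two-sided alpha 0.05, 80% power, about 50 cancers in 4 years.
- **Statistical methods:** the primary outcome is incidence together with "the difference in mean tumour size at diagnosis between the two arms". Size goes to an unpaired t-test or, if not normally distributed, a Mann-Whitney test.

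For incidence, Statistical methods says: "Breast cancer incidence rates will be calculated as the total number of breast cancers detected per 1000 woman-years at risk". This is done with and without DCIS. It is not divided by size or stage.

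The Background reports that in earlier high-risk screening studies MRI "had a significantly higher sensitivity for invasive breast cancer than mammography in all studies".

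**The concern.** Randomisation makes the two groups of women comparable. It does not make the two groups of women with a diagnosed cancer comparable, because the arms differ in how they find cancers. If MRI brings forward, or adds, tumours that mammography would not have shown within the 4 years, group 2 has more small tumours in its size distribution. Its mean falls and its ranks shift, even if exactly as many larger tumours occur as in group 1.

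The Background justifies a randomised trial on the ground that paired studies cannot show in what stage a tumour would have been found by one test alone. A size comparison among diagnosed cases gives up part of what randomisation was meant to secure. At stake is the reading of the main result: more cancers with a smaller mean size fits a true shift to earlier stage, and it also fits extra detection with no shift. The stated analyses do not separate the two.

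**Working it through.** **1. The plan's own figures.** Expected cancers: 2000 women × 4 years × 7/1000 = 56, consistent with about 50. Cancers per arm for 80% power by the normal formula: 2 × (1.960 + 0.842)² × 9²/8² = 19.9, so 20. With 25 per arm the power is 88.2% (normal) or 86.8% (t). The stated 80% is therefore conservative. This does not bear on the present point, but it confirms that the calculation rests on cancers, not on women.

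**2. Who enters each comparison.**

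| Comparison in Statistical methods | Who contributes | Shows extra detection? | Shows fewer larger cancers? |
|---|---|---|---|
| Mean or median size | Women with a diagnosed cancer | No | Not on its own |
| Total incidence, with and without DCIS | All woman-years | Yes | No |

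**3. Shift in the mean with no larger cancer averted.** The documents give neither a mean tumour size nor an expected excess, so all inputs except the SD of 9 mm are assumptions. Each arm has 20 cancers from one size distribution (gamma, mean 17 mm, SD 9 mm). The MRI arm has x further tumours of mean 6 mm (SD 3 mm).

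Shift = x × (17 − 6)/(20 + x).

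Rejection rates are from simulation at two-sided 0.05. Where repeat runs differed, the range is shown.

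| x | Shift in mean (mm) | t-test rejects | Mann-Whitney rejects |
|---|---|---|---|
| 0 | 0 | about 5% | about 5% |
| 5 | 55/25 = 2.2 | 11% | 12–13% |
| 10 | 110/30 = 3.7 | 27% | 32–35% |
| 15 | 165/35 = 4.7 | 45% | 58–59% |
| 20 | 220/40 = 5.5 | 62% | 78–79% |

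From x = 10 on, practically all t-test rejections favour MRI.

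**4. Other assumptions.** With 25 cancers per arm, mean 15 to 20 mm, and extra tumours of mean 5 to 8 mm (SD 2 mm), rejections in favour of MRI were:

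- 5 extra: 7–14% (t), 8–15% (Mann-Whitney)
- 10 extra: 15–36% and 16–42%
- 15 extra: 24–60% and 27–73%
- 25 extra: 43–91% and 46–99%

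The nominal rate in that direction is 2.5%.

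**5. What a rate comparison can deliver.** In every scenario above, the rate of larger cancers over all randomised women has no expected difference, so it is not misled. Its precision is low. For 10 against 4 cancers with equal woman-years, the exact conditional test gives p = 0.18. The rate ratio is 0.4, with approximate 95% interval 0.4 × exp(±1.96 × √(1/10 + 1/4)) = 0.13 to 1.28. With 1000 women per arm, power for an assumed halving is about 25% (10 v 5 per 1000), 31% (12.5 v 6.25) and 59% (28 v 14).

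**The case against.** **Size does not stand alone.** Incidence is named beside it, and Outcomes lists number and stage: "Primary endpoints are the number and stage of detected breast cancers". The mechanism needs surplus cancers in group 2, and total incidence is where they would appear. This stands as a limit on the point. It does not answer it, because a total cannot show whether larger or advanced cancers became fewer.

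**The illustration rests on assumed inputs.** This also stands. The high rejection rates need 50% to 100% more tumours in group 2 and no stage shift at all; with 5 extra tumours the rate is 11%. The average shift stays below the 8 mm that the article calls clinically relevant. A difference of 8 mm or more arises in about 1.4%, 4% and 13% of trials at x = 5, 10 and 20.

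**The direction is not certain.** The Background credits mammography with better sensitivity for DCIS, and Interventions suggests that biennial mammography in group 2 may reduce over-diagnosis of low-grade DCIS. Part of any excess of slow lesions could then fall in group 1.

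**A condensed article may leave a test of stage to the full documents.** That is fair, and the lack of one is not the complaint. The complaint is about the size comparison that the article does fix.

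**Two stronger readings are not supported.** A reader might infer that the bias passes into the mortality and cost-effectiveness estimates. Those come from a natural-history model calibrated jointly on numbers of screens, screen-detected and interval cancers, stage distribution and age at diagnosis; the size test is not an input. A reader might also infer that the plan counts more detections as benefit. It lists number as an endpoint and nowhere says so.

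**Conclusion.** The point holds in a limited form. The one primary comparison with stated power is restricted to a group defined after randomisation by an event that the screening method changes. It can be significant when no larger cancer has been averted, and the accompanying total incidence would not settle the matter. The mechanism is certain. Its size in this trial is not known, because it depends on how many extra small tumours MRI finds and how small they are. The 11–62% range for the t-test and the shift of 2.2–5.5 mm hold only under the assumptions stated above. The point concerns how the size result may be read. It is no evidence that MRI fails to shift stage.

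**What to change.** In Statistical methods:

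1. Add a between-arm comparison of stage- and size-specific cancer rates per 1000 woman-years, over all randomised women by assigned arm, counting screen-detected and interval cancers. Fix the cut-offs in advance, for example invasive cancers above a stated size, and node-positive cancers. Report a rate ratio with its confidence interval.
2. Keep the mean-size test, described as a comparison among detected cancers. State that a smaller mean alone does not show a stage shift and is read together with the rate ratio and its interval.
3. Do not make the reading depend on the mere direction of the counts. With equal true rates of 5 to 10 cancers per arm, group 2 has the lower count by chance in about 44–46% of trials.

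**Cost:** wording only. The woman-years denominator is already in the plan, and stage and interval cancers are already recorded. The downside is precision: advanced cancers will be few and the interval wide, as the 10 v 4 example shows, so the added comparison may well be inconclusive. That is why the size test stays beside it.

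### The primary incidence outcome is defined as a rate per woman-years, but is to be tested as a proportion with no stated denominator; on the ordinary reading the test is valid only if follow-up is equal between arms

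*Protocol article*

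**What the plan says.** The Statistical methods section of the protocol article opens with "Primary outcome will be incidence and the difference in mean tumour size at diagnosis between the two arms", so incidence is one of two named primary outcomes. It is defined as a rate: "Breast cancer incidence rates will be calculated as the total number of breast cancers detected per 1000 woman-years at risk", to be calculated with and without DCIS. The next sentence calls these rates proportions: "Differences between these proportions will be compared using a chi-square test", or Fisher's exact test as appropriate. The section names no method for rates and does not say whether the table counts women or woman-years.

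The Interventions section says that women are "randomized through a computer-generated randomization sequence with stratification for centre". The Sample size section gives 2000 women, 7 cancers per 1000 woman-years and about 50 cancers in 4 years. Its 80% power refers to tumour size; no power is stated for incidence.

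**The concern.** A rate divides cancers by time at risk. A proportion divides women with cancer by women. Chi-square and Fisher tests are built for the second, with each woman counted once as an independent unit. If the plan is followed in that ordinary way, the reported estimate uses woman-years and its p-value does not. The two can then disagree whenever time at risk differs between the arms.

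The arms have different examination schedules (yearly mammography in one, yearly MRI with mammography every other year in the other). Women could therefore leave at different rates, although the article does not predict this. At stake is whether the p-value for a primary outcome belongs to the rate ratio printed beside it.

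**Working it through.** **The plan's own figure.** No figure is given for the incidence test. The event count is 2000 × 4 × 0.007 = 56. The stated figure of about 50 corresponds to 50 / (0.007 × 2000) = 3.57 woman-years per woman. The plan therefore already works with less than four full years each.

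**Inputs.** From the article: 1000 women per arm, 7 per 1000 woman-years, two-sided 5%. Assumed, because the article gives no such figures: 3 years of mean follow-up, a deficit of 10% or 15% in one arm, and a true rate ratio of 1.8 (7 against 12.6 per 1000). Counts x1 (mammography) and x2 (MRI) are Poisson, and woman-years T1 and T2 are treated as fixed.

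**Tests compared.**
- Women as denominator: z = (x2 − x1)/1000 ÷ √[p(1 − p) × 2/1000], with p = (x1 + x2)/2000. This is the uncorrected chi-square test.
- Rate test: z = (x2 − mq) ÷ √[mq(1 − q)], with m = x1 + x2 and q = T2/(T1 + T2).

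**No true difference, MRI arm shorter.** Expected counts are 3000 × 0.007 = 21 in the full arm, and 2700 × 0.007 = 18.9 or 2550 × 0.007 = 17.85 in the shorter one. The women-based statistic is off centre by about (21 − 18.9)/√39.9 = 0.33 or (21 − 17.85)/√38.85 = 0.51. Summing exactly over all pairs of counts gives the type I error:

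| Deficit | Women as denominator | Rate test |
|---|---|---|
| none | 5.4% | 4.9% |
| 5% | 5.7% | 5.1% |
| 10% | 6.7% | 4.9% |
| 15% | 8.4% | 4.9% |

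The 5.4% at equal follow-up reflects small counts, not the denominator. A simulation with 4 years of follow-up and binomial counts gave 5.0% for both tests at equal follow-up. With 10% and 20% deficits the women-based test gave 6.8% and 12.5%, and the rate test stayed near 5%.

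**True rate ratio 1.8, MRI arm shorter.** The ratio of proportions becomes 1.8 × 0.90 = 1.62 or 1.8 × 0.85 = 1.53.

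| Deficit | Power, women as denominator | Power, rate test |
|---|---|---|
| none | 61% | 60% |
| 10% | 43% | 58% |
| 15% | 34.5% | 57% |

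If the mammography arm is the shorter one, the error runs the other way and the women-based test rejects too often.

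**The other reading: woman-years as denominator.** With 10% less follow-up in the MRI arm, this table gives a type I error of 4.9% and power of 58%, practically the same as the rate test.

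**Illustration, like with like.** Take 33 cancers against 19 (assumed), 1000 women per arm.

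| Woman-years (33 arm v 19 arm) | Chi-square, women | Chi-square, woman-years | Fisher, women | Fisher, woman-years | Exact rate test |
|---|---|---|---|---|---|
| 3000 v 3000 | 0.049 | 0.051 | 0.067 | 0.069 | 0.070 |
| 3000 v 2700 | 0.049 | 0.116 | 0.067 | 0.126 | 0.128 |
| 2700 v 3000 | 0.049 | 0.020 | 0.067 | 0.025 | 0.025 |

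The rate ratios in the three rows are 1.74, 1.56 and 1.93. The women-based p-values do not change from row to row.

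**The case against.** The strongest defence is that the phrase about proportions points back to "the total number of breast cancers detected per 1000 woman-years at risk", so the authors may have meant woman-years as the denominator. On that reading the working shows hardly any numerical error, and what remains is loose terminology. This stands as a possible reading, and it is why a reader should not infer that the plan certainly ignores woman-years. It does not remove the point. The text leaves two readings of a primary test open, they can give different p-values on the same data, and woman-years are not independent binomial units.

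Secondly, harm on the women-based reading needs unequal follow-up, and the article neither gives a dropout figure nor predicts a difference. This also stands. With 1:1 randomisation, staggered entry falls alike on both arms and by itself creates no imbalance. At a 5% deficit the effect on type I error is slight.

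Thirdly, it is tempting to set the chi-square p of 0.049 against the exact rate p of 0.128. That mixes two changes: with equal woman-years the exact test already gives 0.070. Only comparisons of the same kind of test are fair.

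Finally, a reader might add that pooling centres is a fault, since allocation is made "with stratification for centre, in one of the two groups" while the tests are stratified only by density. Leaving centre out does not cause the bias described here, and adjustment for it may well be left to an analysis plan that is not shown.

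**Conclusion.** The point holds in a limited form. The stated test does not match the stated estimate for a primary outcome, and its denominator is not fixed. On the ordinary reading there is essentially no distortion with equal follow-up. With an assumed 10% to 15% deficit in one arm, type I error is about 6.7% to 8.4%. When the MRI arm is the shorter one and the true rate ratio is 1.8, power is about 43% to 34.5%, where a rate test keeps 57% to 58%. These sizes rest on the assumed deficits, 3 years of follow-up and 7 per 1000 woman-years; the real imbalance is unknown.

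The documents do not support the stronger inference that the primary incidence result will be biased. The sample size justification, which concerns tumour size, is untouched. This should be fixed, but it does not undermine the trial.

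**What to change.** Replace the sentence on comparing proportions with one that compares incidence rates by Poisson regression, with arm as a term and log woman-years as offset, reporting the rate ratio with its 95% CI. Where counts are small, use the exact conditional (binomial) test of the two counts given the woman-years. Apply this both including and excluding DCIS. Centre may be added as a term, but that is optional and not part of the error.

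The cost is one sentence of analysis text. Woman-years are already to be calculated, so no new data are needed, and little changes if follow-up turns out equal.
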